#### Primary outcome measure

The primary outcome is the rate of a composite of maternal mortality, major maternal morbidity and fetal losses (with no double counting) occurring during pregnancy, labour or within 42 days of delivery, including at least one of:Maternal death (all-cause mortality)Eclampsia (occurrence of generalised convulsions with increased blood pressure in the absence of epilepsy or another condition predisposing to convulsions)Emergency hysterectomy (surgical removal of all or part of the uterus)Stillbirth (born without signs of life at or after 28 weeks of gestation)

The primary outcome measures will be assessed by the numbers of events reported at the district (or referral) hospital and the peripheral health units offering the highest level of care (defined as the 20% with the highest level facilities in each district).

#### Secondary outcome measures

Maternal deaths from all-cause mortality will be collected. Additional information will be collected regarding the cause of death, including deaths due to:Any obstetric causeObstetric haemorrhagePregnancy-related sepsisHypertensive disorders of pregnancy

Additional secondary maternal outcome measures will include:5.Eclamptic fit before hospital admission6.Eclamptic fit after hospital admission7.Emergency hysterectomy due to obstetric haemorrhage8.Emergency hysterectomy due to ruptured uterus9.Emergency hysterectomy due to other cause

#### Perinatal secondary outcomes

Earlier recognition of pregnancy hypertension during antenatal care should facilitate appropriate timing of delivery and reduction in preventable stillbirth and neonatal morbidity and mortality as a complication of preeclampsia and eclampsia. Conversely, extreme preterm delivery to reduce maternal morbidity and mortality from preeclampsia/eclampsia may result in an increase in neonatal mortality. Therefore, perinatal secondary outcomes will include:10.Antenatal stillbirth11.Intrapartum stillbirth12.Stillbirth beyond 28 weeks’ gestation13.Early neonatal death (before seven days)14.Late neonatal deaths (seven to 28 days)

The CRADLE intervention should enable healthcare professionals to recognise abnormal vital signs earlier and manage complications in a timelier manner, with the management of severely compromised pregnant women potentially requiring transfer to higher-level centres for specialist treatment. Normal vital signs should reassure clinicians and reduce inappropriate referrals. Secondary referral outcomes will include an analysis of the National Emergency Medical Service (NEMS) routine database. However, this data will only be analysed if the NEMS data is consistently collected during the entire trial period. Additional outcomes may include:15.Total number of obstetric referrals16.Number of referrals related to hypertensive disorders of pregnancy17.Number of referrals related to eclampsia18.Number of referrals related to obstetric haemorrhage19.Number of referrals related to pregnancy-related sepsis

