## Introduction: background and rationale {6a}

In Sierra Leone (SL), the reduction of maternal and neonatal morbidity and mortality are high priorities of the health sector, in line with the third Sustainable Development Goal [1]. Despite an almost 40% reduction in the maternal mortality ratio (MMR) from 1165 per 100,000 in 2013 to 717 per 100,000 live births in 2019 [2], SL still has one of the highest MMR in the world. One in thirty-one women die during childbirth [3], with a 40 to 60 percent higher risk for teenage mothers [4]. Perinatal mortality is high (34 per 1000 live births), with a stillbirth rate of 24 per 1000 live births [3]. Infants whose mothers die are up to ten times more likely to die within the first two years of life [5].

Data from the CRADLE-3 trial [6] correlate with national statistics; 76% of maternal deaths are caused by haemorrhage, hypertension and sepsis [7]; all of which are marked by abnormalities in blood pressure (BP) and heart rate (HR). If deteriorating vital signs are detected early, maternal morbidity and mortality are preventable with simple, cost-effective interventions that are widely available in SL [6, 8]. However, there are often disparities in access to vital sign assessment and skilled intervention, and delays in delivery and escalation of care [9, 10], varying by geographical area and socio-demographic characteristics.

Vital sign measurement is an international standard part of maternity care. The CRADLE Vital Sign Alert (VSA) device is a hand-held, semi-automated, low-cost BP and HR measuring device with a built-in traffic-light warning system that has been especially developed for use in low-income settings during pregnancy and the postpartum period [11]. The device has additionally been validated as accurate for use in women with preeclampsia [12] and in those who develop low BP from sepsis or haemorrhage [13].

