## Objectives {7}

The primary objective of the trial is to determine whether real-world scale-up of the CRADLE VSA device and focused education package to community and facility level maternity care in SL is sustainably adopted and reduces a composite of (all-cause) maternal mortality or major morbidity and fetal loss by ≥ 20%.

The trial is complemented by a simultaneous process and scale-up evaluation informed by Medical Research Council guidance [17] and WHO ExpandNet tools [16]. The specific goals of the process and scale up evaluation are to (1) analyse how, and to what extent, the CRADLE intervention has been implemented, (2) assess how the different contexts can influence the implementation process and scale-up strategies and (3) assess the process and sustainability of the scale-up. This will include an evaluation of cost-effectiveness.

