#### Component 2—CRADLE Training programme

A face-to-face training programme will be rolled out to a selected sample of locally selected CRADLE champions, district stakeholders and key maternal health partners in the district headquarter towns by the central CRADLE team, comprising two senior midwives and the program manager. The training package is as described below but can be adapted to meet specific contextual factors. It includes a short, animated video describing the device and how it is used (https://cribs-i.org/professionals/cradle-vsa/microlife-cradle-vsa-user-guide/), an interactive session with the trainees, a reference booklet, a wall poster showing how the device is used and an aide-memoire card attached to the CRADLE device for quick reference. The animated film is in English and has also been translated into Krio, the most commonly spoken language across Sierra Leone. The content of this training material covers: (1) use of the Microlife CRADLE VSA device, (2) basic clinical assessment of pregnant women, (3) understanding pre-eclampsia, eclampsia, obstetric haemorrhage and sepsis and review of local management guidelines and protocols, (4) triggers for treatment and/or referral and familiarisation with local referral pathway, (5) CRADLE VSA device troubleshooting and (6) CRADLE VSA maintenance manual.

Components of the training have been adapted to meet the SL specific contextual needs: the training was expanded to include a more extensive focus on Emergency Obstetric and Newborn Care (EmONC) training as well as an increased focus on community engagement, training facilitation tips, respectful maternity care and a CRADLE maintenance practical session. A training aide in the form of the CRADLE song, to a local popular tune, was integrated.

Champions were encouraged to follow the ten-step training content approach:Explain CRADLE (CRADLE video)Explain the traffic lightsExplain the arrowsExplain the different scenarios and their managementPractical demonstration of how to use the deviceExplain respectful maternity care and role play to communicate CRADLE results with womenDemonstrate how to document the CRADLE resultsPractical session using the CRADLE observation checklistExplain how to maintain CRADLE and explain the “Replace & Repair” systemSing the CRADLE Song

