### Adverse event reporting and harms {22}

Blood pressure and pulse measurement is standard practice as a screening tool in antenatal care and therefore no adverse events or harms are expected.

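### The primary composite counts stillbirth but not neonatal death, and no listed outcome combines the two, so a stillbirth that becomes an early neonatal death could be read as benefit

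*Protocol article*

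**What the plan says.** **Primary outcome.** Primary outcome measure defines the endpoint as "a composite of maternal mortality, major maternal morbidity and fetal losses (with no double counting"). It has four components: maternal death, eclampsia, emergency hysterectomy and "Stillbirth (born without signs of life at or after 28 weeks of gestation"). Neonatal death is not among them. Objectives {7} words the aim to match: the question is whether the intervention "reduces a composite of (all-cause) maternal mortality or major morbidity and fetal loss by ≥ 20" per cent.

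**Expected effects on the baby.** Perinatal secondary outcomes gives the hoped-for direction first: "Earlier recognition of pregnancy hypertension during antenatal care should facilitate appropriate timing of delivery and reduction in preventable stillbirth and neonatal morbidity and mortality". The counter-risk follows: "Conversely, extreme preterm delivery to reduce maternal morbidity and mortality from preeclampsia/eclampsia may result in an increase in neonatal mortality". For that stated reason the section lists antenatal, intrapartum and all stillbirth from 28 weeks (outcomes 10 to 12), then early and late neonatal death (outcomes 13 and 14). Each stands alone.

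**Analysis.** Statistical methods {20a} has every component of the composite analysed in the same way as the composite. That covers stillbirth but not neonatal death. Outcomes {12} gives all outcomes the same denominator, deliveries in the district and six-week period.

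**The concern.** The protocol says the intervention works partly through the timing of delivery. When timing changes, whether a baby who dies is recorded as a stillbirth or as a neonatal death can change too. The first counts in the primary outcome and the second does not, so such a change lowers the primary rate although the baby still dies.

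Analysing the components separately would not reveal this: stillbirth would simply appear to improve. A reader would have to set outcome 12 against outcome 13 and judge the net effect by eye, with no estimate or confidence interval for the sum. What is at stake is the conclusion about babies. A fall in the composite driven by stillbirth could be reported as benefit when perinatal deaths had not fallen, or a real benefit could look larger than it is.

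**Working it through.** **Inputs from the protocol**
- Composite rate 5% falling to 4%, eight districts, about 1000 deliveries per district and six-week period, cluster autocorrelation (CAC) 1 (Sample size estimation {14}). The target is thus a fall of 50 − 40 = 10 per 1000.
- National rates, from Introduction {6a}: "Perinatal mortality is high (34 per 1000 live births), with a stillbirth rate of 24 per 1000 live births".

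**Assumptions, not in the documents**
- Stillbirth is 2.4% of trial deliveries. The national figure is per live births; per birth it would be 24/1024 = 2.34%. The rate in the sampled facilities may differ more than that.
- Early neonatal death is 34 − 24 = 10 per 1000.
- A share *f* of stillbirths becomes early neonatal deaths, with *f* = 10%, 20% or 30%, and no baby is saved.
- No affected woman has another component event.

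**Step 1: reproduce the plan's power.** I used the Hussey–Hughes variance with CAC 1:

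Var = Iσ²(σ² + Tτ²) / [(IU − W)σ² + (U² + ITU − TW − IV)τ²]

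Here σ² = (1 − ICC)·p(1 − p)/1000, τ² = ICC·p(1 − p), and p is the mean of the two rates. U is the number of treated district-periods; W and V are the sums of squared period totals and squared district totals. With eight steps and nine periods, I = 8, T = 9, U = 36, W = 204, V = 204. For 5% against 4%, p = 0.045.
- ICC 0.5: SE = 0.00192; 0.01/0.00192 − 1.96 = 3.25; power 99.9%. The protocol's figure of nearly 100% is reproduced.
- ICC 0.01: SE = 0.00269; 0.01/0.00269 − 1.96 = 1.76; power 96%.
- If Falaba and Bonthe cross together (seven steps, eight periods), power is 99.8% and 94%.

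**Step 2: a pure shift in the present composite.** Rate = 50 − 24*f* per 1000.

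| *f* | Largest fall per 1000 | Share of target | Risk ratio | Chance of a significant result, ICC 0.01 to 0.5 | Early neonatal death per 1000 | Power to detect that rise, ICC 0.01 |
|---|---|---|---|---|---|---|
| 10% | 2.4 | 24% | 0.95 | 14% to 22% | 12.4 | 42% |
| 20% | 4.8 | 48% | 0.90 | 41% to 68% | 14.8 | 92% |
| 30% | 7.2 | 72% | 0.86 | 75% to 96% | 17.2 | over 99% |

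The table uses eight steps. With the pair crossing together, the chances at ICC 0.01 are 12%, 37% and 70%. To imitate the whole 20% reduction by shift alone, *f* must be 10/24 = 42%. If stillbirth were 30 or 40 per 1000, *f* would be 10/30 = 33% or 10/40 = 25%.

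**Step 3: the combined outcomes.** Under a pure shift, perinatal death is (24 − 24*f*) + (10 + 24*f*) = 34 per 1000 whatever *f* is. The composite with early neonatal death added starts at 50 + 10 = 60 per 1000, assuming no overlap, and stays there, so the risk ratio is 1.00. Power for a real fall from 6% to 5% is 92% (ICC 0.01) to 99.7% (ICC 0.5) with eight steps, and 89% to 99.4% with the pair.

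The probabilities are model-based approximations, not the planned permutation test, and rest on the protocol's CAC of 1.

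**The case against.** The strongest reply is that the protocol saw the risk and acted on it. Neonatal deaths are secondary outcomes for exactly this reason, on the same denominator as stillbirth. The composite also matches its objective, which speaks of fetal loss. Both points stand: the gap lies in what the primary result can show and in the absence of a combined outcome, not in the data collected. For larger shifts the early neonatal outcome would probably reveal the rise if deaths were fully recorded; for a 10% shift it has only about 42% power.

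The sizes are also open to attack, and rightly. No shift is quantified in the documents, the warning concerns pre-eclampsia and eclampsia rather than all stillbirths, and the 5% rate has no breakdown. Because each woman counts once, a mother who also has eclampsia or a hysterectomy, or who dies, stays in the composite. The falls in the table are therefore upper bounds for the assumed stillbirth rate.

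It may be said that a combined outcome belongs in an analysis plan. Rules of interpretation may well. But this article sets out the outcome list, and an added outcome belongs there.

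A reader might infer more than the text supports:
- **That the protocol expects deaths to move past birth.** It does not. It expects falls in both stillbirth and neonatal mortality, and calls a neonatal rise possible. An added neonatal death after delivery for the mother's sake need not replace a stillbirth.
- **That the newborn-care training is a stated route for such a shift.** The training section says only that "the training was expanded to include a more extensive focus on Emergency Obstetric and Newborn Care (EmONC) training". It does not mention changing stillbirths into live births.
- **That the harms section contradicts the warning.** Its statement that "therefore no adverse events or harms are expected" concerns blood pressure and pulse measurement, not later delivery decisions. The scopes differ, so no clear contradiction is shown.

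**Conclusion.** The point holds as a cheap improvement. The primary composite cannot register a rise in neonatal death that the protocol itself names as possible, and a stillbirth that becomes an early neonatal death could lower the primary rate with no life saved. No listed outcome nets the two.

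The size is unknown. At an assumed stillbirth rate of 2.4% of deliveries and an assumed shift of 10% to 30%, the composite would fall by at most 2.4 to 7.2 per 1000 against the 10 per 1000 target. Reproducing the whole target would need a 42% shift, or 25% to 33% at the higher assumed stillbirth rates. The documents do not support inferring that a positive primary result would probably be an artefact, nor that the primary outcome must be replaced.

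**What to change.** Keep the primary outcome. Add two items to the perinatal secondary outcomes, each per delivery, counted once per woman and analysed with the primary model:
1. Perinatal death: stillbirth at or after 28 weeks, or early neonatal death before seven days.
2. The primary composite with early neonatal death before seven days added.

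Report both beside the primary result, and interpret any fall in stillbirth in the light of the perinatal result. An absolute rule barring any claim of fetal benefit unless perinatal death also falls would go too far. Under Plans for assessment and collection of outcomes {18a}, events outside the sampled hospitals and peripheral units are not included, so neonatal deaths at home would be missed. State this as a limitation of both outcomes.

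The cost is a small extra analysis of outcomes already listed for collection. The primary outcome and its sample size do not change.

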### Process and scale up evaluation of the CRADLE intervention

The process and scale-up evaluation of the protocol intervention will be evaluated via a mixed-methods approach (i.e. routine data, qualitative interviews, focus group discussions, direct observations, reporting forms at baseline and set time points) drawing on the Medical Research Council for complex interventions [17]. We will consider the SL context, our theory of change, the engagement and involvement of stakeholders and understanding uncertainties, adoption and costs. To analyse complex issues in the development of the scale-up strategy during this trial, we will use the ExpandNet/WHO scale-up framework to understand how the CRADLE innovation can being taken to scale in the context of four elements; the resource team, user organisations, scale up strategies and strategic choice areas for managing scale-up [16].

The study population for the evaluation are stakeholders involved in the CRADLE intervention rollout development and implementation process and those involved in the policy dialogues. Stakeholders likely to influence implementation include political leaders, external health actors including NGOs and UN agencies, interest groups including medical and midwifery schools, financial decision makers, beneficiaries and community and family players. The study population for the scale-up evaluation is the target population, i.e. healthcare workers, pregnant / postpartum women living in the relevant districts and communities.

Measures [27] include but are not limited to:Fidelity (the number and proportion of facilities that received CRADLE devices, and CRADLE training; the number of devices distributed; the number and proportion of frontline healthcare staff trained in CRADLE; fidelity of CRADLE training);Adoption (training to frontline healthcare workers, number and proportion of blood pressures as per CRADLE training);Adaptations to the CRADLE intervention and implementation process throughout the trial using self-reported district implementation diaries, evaluating policy dialogue through, e.g. a policy lab, contextual factors and implementation strategies, as well as be explored qualitatively;

Scale-up outcomes of reach, maintenance, sustainability and integration will be assessed through triangulation of findings from different measurement tools.Reach will be assessed through GPS-tracked CRADLE training and data collection, pre/post-assessment of blood pressure measurement accuracy (using terminal digit preference); number and appropriateness of referrals before and after CRADLE intervention; timely and accurate escalation of care for women with eclampsia and shock.Maintenance assessment of CRADLE BP measurement will entail a mixed methods pre/post-design audit of CRADLE “repair and replace” strategies; spot checks of training quality over time and care pathways will be interrogated through interviews with implementers and the local and national teams across timepoints to assess how CRADLE implementation has improved or deteriorated across its components.Sustainability will be assessed through reviewing minutes of quarterly stakeholder meetings focused on device maintenance, ongoing training and adoption across different stages of the trial and policy mapping. The policy map will be filled in to reflect change at local and national level. Both will generate a policy timeline on maternity care, to assess how the context influences CRADLEs activities, and vice versa.Progress on integration will be explored through experiences of care pathways for women themselves, healthcare staff and local community stakeholders and ways in which roadmap actions (including interventions, programmes and reforms) should and have been expanded (e.g. integration into national and partner training, procurement and supportive supervisions).

We will explore relationships between process outcomes and the primary outcome to examine whether the effects of the CRADLE intervention differ by implementation. Qualitative work will add deeper understanding of changes in implementation, experiences of the CRADLE package and potential mechanisms to explain initial quantitative results. A combination of both quantitative and qualitative data will be needed to answer our research questions.

### Participant timeline {13}

The participant timeline is presented in Fig. 2.

### Sample size estimation {14}

Sample size estimation has been provided by the CRADLE senior statistician, using Stata version 13.1 and the methods of Hemming and Girling [28]. The power of the study will depend on three factors: (1) the design (eight groups, six-weekly time periods, around 1000 deliveries/period/centre), (2) the event rate and treatment effect (5% falling to 4%) and (3) the data structure, specifically the intraclass correlation coefficient (ICC) and cluster autocorrelation (CAC) coefficients.

Sample size calculations for longitudinal cluster randomised trials, such as our proposed stepped-wedge trials, necessitate the estimation of the correlation structure underlying the study. This entails assessing both the within-period intra-cluster correlations, which differ from conventional intra-cluster correlations due to their reliance on the period, and the cluster autocorrelation coefficients to account for correlation decay. For the purposes of the power calculation, we assume that there are up to 1000 deliveries per district per six weeks (half the 2000 we consider likely), across eight districts, each observed for 12 months. It is difficult to estimate more accurately at present, as we have no suitable multi-centre, multi-time period data in a single low-income country. However, if the ICC is suitably low and the CAC is suitable high, at the time of analysis, we do not predict any difficulties. We will obtain this information from our observational pilot data gathered in January to May 2022 in all eight districts of the study. Feasibility data suggests the CAC is likely to be 1. Therefore, even with an extremely high intra-cluster correlation of 0.5, power would be close to 100%. We have used https://clusterrcts.shinyapps.io/rshinyapp/ for the calculations. As per Fig. 3, with a CAC of 1, power will be more than adequate with 1000 women per month per centre.

**Fig. 3 Fig3:**
[figure not shown]
Demonstration modelling of cluster size calculation if ICC 0.01, 0.02 and 0.5 with CAC = 1

We intend to consider whether the treatment effect can be linked to the extent and quality of the implementation of the intervention in each district, as measured by our implementation and scale-up metrics. An absolute difference of 0.25% in the treatment effect between districts would clearly be important. Given the high power for the main treatment effect, we anticipate that we will have more than adequate power to detect such a difference.

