## Statistical methods

### Statistical methods for primary and secondary outcomes {20a}

This is a type 2 hybrid implementation-effectiveness cluster randomised controlled trial in a stepped-wedge design that will allow us to simultaneously test our clinical intervention in the form of the CRADLE device and the effectiveness of our implementation strategy. This design is based on those described by Hussey and Hughes [29] and Curran et al. [30].

For our primary analysis method, we will use a new approach described by Thompson et al. [31, 32]. For this non-parametric within-period method, Monte Carlo permutation tests for stepped wedge trial designs are employed to calculate the confidence intervals and *P*-values. This is implemented in the Stata command “swpermute” [31]. Based on current statistical theory, this will provide the most accurate and reliable estimates of the intervention effect.

Thompson et al. [31] provide a non-parametric within-period method for correcting the *P*-values (and therefore the standard errors) for a valid regression model. The regression model (binomial, with a log link) that we propose to use will estimate the risk ratio for the effect of the planned intervention. It will include fixed effects for separate linear trends in each region, with a single step at the time the intervention is introduced into the district. As the method is robust to how the correlation structure is specified, further allowances for the data structure, as used in multi-level modelling, are not needed. Odds ratios will be given if models fail to converge when estimating risk ratios. Effects of treatment on primary outcomes will be estimated with 95% confidence intervals and significance at *P* < 0.05. As the primary endpoint is a composite, all the components will also be analysed in the same way. The effect of the intervention on primary and secondary outcomes will be analysed using multilevel logistic regression with random effects of centre and adjustments for fixed categorical effects of time. In addition, we will adjust for the availability of six common drugs: magnesium sulphate (MgSO_4_), ampicillin, gentamycin, metronidazole, oxytocin, and misoprostol, varying with time and district.

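### High power for the main effect does not give adequate power for a 0.25-point difference in effect between districts; on the plan's inputs that power is far too low

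*Protocol article*

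**What the plan says.** The section Sample size estimation {14} of the protocol article builds its power on "eight groups, six-weekly time periods, around 1000 deliveries/period/centre", with the primary event rate falling from 5% to 4%. The 1000 deliveries are described as "half the 2000 we consider likely", and the calculation is "across eight districts, each observed for 12 months". With a cluster autocorrelation coefficient (CAC) of 1, the section reports power close to 100% for the main effect, even at an intraclass correlation (ICC) of 0.5, a value it regards as extreme.

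The text below Fig. 3 then turns to whether the treatment effect varies with the extent and quality of implementation in each district. It says: "An absolute difference of 0.25% in the treatment effect between districts would clearly be important", and continues: "Given the high power for the main treatment effect, we anticipate that we will have more than adequate power to detect such a difference". No separate calculation is given for this contrast. The only reason offered is the power for the main effect.

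The same analysis is announced under Process and scale up evaluation of the CRADLE intervention: "We will explore relationships between process outcomes and the primary outcome to examine whether the effects of the CRADLE intervention differ by implementation".

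**The concern.** Main-effect power concerns a 1.0-point difference estimated from all eight districts. The between-district question concerns a difference one quarter as large, and each side of that contrast draws on only some of the districts. Smaller signal and larger error act together, so power near 100% for the first does not imply adequate power for the second.

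This is a hybrid implementation-effectiveness trial, so the link between implementation quality and effect will attract attention. If a difference of the size called important were real, a non-significant interaction would still be the most likely result. A reader who relies on the published power statement could then take that result as evidence that implementation quality does not matter.

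**Working it through.** **Inputs from Sample size estimation {14}, Fig. 3 and the statistical methods**
- 8 districts; all in control at time point 0, then one crossing per six-week step, giving 9 periods in about 12 months.
- m = 1000 deliveries per district-period, or 2000, the number thought likely.
- Event rate 5% falling to 4%. Variance is taken at the midpoint: 0.045 × 0.955 = 0.0430.
- CAC = 1; ICC = 0.01, 0.02 or 0.5 (the Fig. 3 values).
- Inference "with 95% confidence intervals and significance at *P* < 0.05", taken as two-sided.

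**Model.** Generalised least squares on district-period proportions, with categorical period effects, a random district effect with variance ICC × 0.0430, and residual variance (1 − ICC) × 0.0430 / m. The interaction is treatment × district group, evaluated over all 70 splits of four districts against four. With δ the difference sought, power = Φ(δ/SE − 1.96) + Φ(−δ/SE − 1.96). The difference detectable with 80% power is (1.96 + 0.84) × SE = 2.80 × SE.

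**Step 1. The plan's own figure (main effect, δ = 1.0 point, m = 1000)**
- ICC 0.01: SE 0.269 points; 1.0/0.269 = 3.72; power 96%.
- ICC 0.5: SE 0.192 points; 1.0/0.192 = 5.21; power 99.9%.

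The claim of power close to 100% at ICC 0.5 is reproduced, so the model matches the plan's own calculation.

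**Step 2. Four districts against four, δ = 0.25 points, 9 periods**

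| m | ICC | SE, points (median, range) | δ/SE at median | Power (range over splits) | Detectable at 80% (median) |
|---|---|---|---|---|---|
| 1000 | 0.01 | 0.365 (0.358-0.383) | 0.68 | 10-11% | 1.02 |
| 1000 | 0.5 | 0.262 (0.257-0.275) | 0.95 | 15-16% | 0.73 |
| 2000 | 0.01 | 0.260 (0.254-0.272) | 0.96 | 15-17% | 0.73 |
| 2000 | 0.5 | 0.185 (0.181-0.194) | 1.35 | 25-28% | 0.52 |

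ICC 0.02 gives the same figures as 0.01 to the precision shown.

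**Step 3. Why the inference fails.** At m = 1000 and ICC 0.01 the interaction SE is 0.365/0.269 = 1.36 times the main-effect SE, and the target is 4 times smaller. The ratio of signal to error is therefore 4 × 1.36 = 5.4 times smaller. To reach δ/SE = 2.80 for the interaction, the main effect would need a ratio of about 2.80 × 5.4 = 15. Main-effect power is already near 100% at a ratio of 4 or 5, so it cannot show whether the interaction is adequately powered.

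**Step 4. Two single districts, simple before-after, no time effects.** With 4.5 periods on each side on average, n = 4500 before and after at m = 1000. SE per district = √(0.0475/4500 + 0.0384/4500) = 0.437 points. For the difference of two districts, SE = √2 × 0.437 = 0.62 points, δ/SE = 0.40 and power is 7%. At m = 2000, SE is 0.437 points and power 9%.

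**Step 5. Sensitivity (four against four)**
- Longer window. Trial status includes outcomes from 23 May 2022 to 1 January 2024: 588 days / 42 = 14 periods. Assuming the same steps and a longer post-intervention phase, power is 13-14% (m = 1000, ICC 0.01), 20-24% (m = 2000, ICC 0.01) and 35-42% (m = 2000, ICC 0.5).
- Falaba and Bonthe crossing together (7 steps, 8 periods): 9-10% (m = 1000, ICC 0.01), 13-15% (m = 2000, ICC 0.01) and 21-25% (m = 2000, ICC 0.5).
- A separate linear trend per district, close to the planned regression model: 7% (m = 1000) and 9% (m = 2000), ICC 0.01.
- Deliveries needed at ICC 0.01 over 9 periods: median power is 75% at 15,000 per district-period and 86% at 20,000, so 80% lies between them.

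The section also mentions 1000 women per month. That is about 1440 per six weeks, between the two sizes tested.

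**The case against.** The best defence has four parts.

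*The wording is tentative.* The plan intends to consider this question, anticipates power, and elsewhere speaks of exploring. Effect modification by implementation is not in the primary objective or among the three numbered process goals, and the primary test and sample size do not rest on the sentence. This stands, and it lowers the severity. It does not rescue the sentence, which names a difference, calls it important and gives an invalid reason for expecting to detect it.

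*The contrast is undefined.* The text does not say whether it means a pair of districts, groups of districts or a gradient on a score; four against four is an assumption made here. This stands, so no single power figure is exact. Across the readings of a 0.25-point gap that were tested over 12 months (one against one, one against seven, four against four, lowest to highest on a linear score), power runs from about 6% to 28%. Conventional power is approached only by substituting another quantity, 0.25 points per standard deviation of an implementation score. That is about 0.76 points from lowest to highest district, and it gives 62-86% with both 2000 deliveries and ICC 0.5, but 21-33% at 1000 and ICC 0.01. The text does not describe that quantity.

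*Low-ICC, 12-month figures understate the upper end.* A reader might infer that power cannot exceed about 16%, or that the standard error always exceeds the 0.25 points sought. The documents do not support either as a general statement. At 2000 deliveries and ICC 0.5 the standard error is 0.18-0.19 points and power 25-28%. With 14 periods and 2000 deliveries it is 0.20-0.22 points even at ICC 0.01.

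*No conclusion of no difference is planned.* This is correct. The process evaluation says that quantitative and qualitative data will be combined. Misreading a null result is a risk that the power statement creates, not something the protocol proposes.

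**Conclusion.** The concern holds. The claim of more than adequate power is unsupported by the reason given and is contradicted by the plan's own inputs. For four districts against four over nine periods, power is about 10-11% at 1000 deliveries and 15-17% at 2000 when the ICC is 0.01-0.02. It reaches 25-28% only with 2000 deliveries and ICC 0.5, and at most about 42% if the window runs to January 2024 as well. No tested reading of a 0.25-point gap comes near 80%.

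These figures assume CAC 1, a normal approximation that is generous with eight clusters, and the contrast stated. The planned permutation inference would not be expected to raise them.

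A reader might also infer that the trial is underpowered for its primary outcome. This check does not show that: under the same assumptions the main-effect power is 96% or more in the one-district-per-step design. The point should be fixed, but the primary conclusion does not depend on it.

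**What to change.** - Delete the sentence claiming more than adequate power for the between-district difference.
- State that a 0.25-point difference is not reliably detectable, and define the contrast meant by a difference between districts.
- Give the detectable difference conditional on that contrast, the ICC, the cluster-period size and the number of periods. For four districts against four over nine periods with 80% power, it is about 1.0 point at 1000 deliveries and 0.7 at 2000 with low ICC, and about 0.5 at 2000 with ICC 0.5.
- Label the implementation-by-effect analysis exploratory. Report it as an interaction estimate with a 95% confidence interval, and state that a non-significant result will not be read as no difference.

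The change is to wording only. Its one cost is a less favourable stated figure; design, data collection and primary analysis stay as they are.
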